### Participant Retention

Research assistants will make every reasonable effort to follow participants for the entire study period. The research team has developed standard operating procedures to promote participant retention and complete follow-up; researchers attempt to contact participants up to 10 times via telephone and email for a period of 4 weeks before the participant is deemed lost to follow-up.

### Safety Considerations

While ACE is considered safe according to the protocol outlined here, as a precaution participants in the intervention groups are instructed to stop ACE if they experience prolonged or frequent uterine contractions, vaginal bleeding, or feel unwell, and to notify their healthcare provider before continuing ACE. Participants are advised to contact their relevant hospital if they experience reduced fetal movements, and cease expressing until reviewed. Intervention group participants are monitored for any risks based on the participant’s activity in the expressing diary.

### Harms

If a participant reports a notable adverse event, like physical harm to their pregnancy possibly resulting from ACE, they will be withdrawn from the trial and be advised to seek immediate medical attention. In addition, if any participant reports any emotional upset or distress from being unable to express colostrum in pregnancy, they will be contacted by a researcher. The researcher will reassure the participant that not all individuals can collect colostrum in pregnancy, and this does not predict breastfeeding success. If the participant continues to express feelings of distress they will be withdrawn from the trial and advised to seek medical or therapeutic support from their preferred practitioner. The ACE Study researchers will immediately report any serious or unexpected adverse events on participants to the HREC at ECU.

## Outcomes/Measurement

Details of the primary and secondary outcome measures are provided in Table 4. In addition to recording data related to the primary and secondary outcomes, infant admission to the special care nursery (SCN), gestational age at birth, the post-term induction rate and time from starting ACE (obtained from expressing diaries) until going into labor will be recorded for MW and VI group participants to determine if ACE influences these additional outcomes.

**Table 4. table4-08903344231215074:** Details of the Outcome Measures Used in the ACE Study.

Outcome Measure	Measurement	Details of Measure
Primary outcome		
Exclusive breastfeeding at 4 months postpartum (EBF4M)	4-month postpartum questionnaire	Difference, between the control group and intervention groups combined (MW and VI), in the proportion of infants EBF4M
Secondary outcomes		
Exclusive breastfeeding during the initial hospital stay	Use of human milk substitutes in the hospital (medical records), 1- week postpartum questionnaire	Difference, between the control group and the intervention groups (MW and VI), in the proportion of infants exclusively breastfed in hospital
Exclusive breastfeeding at 1, 4, 8, 12 and 16 weeks postpartum	Postpartum questionnaires	Difference, between the two (MW and VI) groups, in the proportion of infants exclusively breastfed at 1, 4, 8, 12 and 16 weeks
Secretory activation (SA)	1- week postpartum questionnaire	Difference, between the control group and intervention groups (MW and VI), in the proportion of mothers who have SA at ≤ 1 day, 2-3 days, or >3 days
Colostrum composition after birth	Colostrum analysis: Macronutrients, EGF, IgA, soluble CD14, Lactoferrin and TGF	Difference, between the control group and intervention groups (MW and VI), in post-birth colostrum composition *(optional component for participants who opt-in only)*
Other outcomes		
Maternal attitudes to infant feeding	Iowa Infant Attitude Scale (IIFAS)	Difference, between the control group and intervention groups combined (MW and VI), scores on the IIFAS
Breastfeeding self-efficacy	Breastfeeding Self-Efficacy-Short-Form (BSES-SF)	Difference, between the control group and intervention groups combined (MW and VI), in BSES-SF scores
Post-term induction rate	Medical data	Difference, between the control group and intervention groups combined (MW and VI) in post-term induction rate
Time from starting ACE (obtained from expressing diaries) until labor	Expressing diaries/medical data	Difference, between the control group and intervention groups combined (MW and VI) in time from starting ACE until labor
Gestational age at birth	Medical data	Difference, between the control group and intervention groups combined (MW and VI) in gestational age at birth
Infant admission to SCN	Medical data	Difference, between the control group and intervention groups combined (MW and VI) in the proportion of infants admitted to the SCN

*Note*. ACE = antenatal colostrum expression; MW = midwife; VI = video instruction; SA = secretory activation; SCN = special care nursery; IgA = Immunoglobulin A; EGF = epidermal growth factor; TGF = transforming growth factor; MAQ = mothers’ antenatal questionnaire; IIFAS = Iowa Infant Feeding Attitudes Scale; BSES-SF = breastfeeding self-efficacy – short form.

Potential confounders identified a priori include maternal education, BMI, smoking, living in cities (Moss et al., 2020), maternal attitudes towards breastfeeding (Cox et al., 2015), and paternal breastfeeding support (Davidson & Ollerton, 2020).

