### Exclusion Criteria

The exclusion criteria are listed in Table 1. Individuals who develop any relevant maternal or infant medical conditions listed as exclusion criteria will not be eligible to participate/will be withdrawn from the trial.

**Table 1. table1-08903344231215074:** PICO (Population, Intervention, Comparison, Outcomes) for the ACE Study.

Study Component	Details
Population	Inclusion criteria
	● Nulliparous individuals
	● Singleton pregnancy
	● Able to read and speak in English
	● Planning to breastfeed
	● Willing to participate in the trial
	● Planning to give birth at one of the trial sites
	Exclusion criteria
	● EPDS score ≥13, or PASS score ≥26
	● Diabetes (pre-existing and pregnancy-induced)
	● Pre-eclampsia
	● Placenta previa
	● Antepartum hemorrhage
	● History of threatened/actual premature labor
	● Cervical incompetence
	● Fetal anomaly (cleft palate, down-syndrome, heart defect, neural tube defects)
	● Fetal compromise (polyhydramnios, known inter-uterine growth restriction)
	● Preterm birth (<37 weeks gestation)
Intervention	Intervention components in addition to standard maternity care during phase 2 include:
	● Oral and written information on antenatal colostrum expression: commence hand expressing from 37 weeks gestation, twice a day for 3-5 minutes per breast (maximum 10 minutes); and information on safe storage of colostrum during pregnancy
	● One-on-one ACE education session with midwife/IBCLC *or*
	● Unlimited access to an online 16-minute ACE instructional video
Comparison	Control group will receive standard maternity care
Outcomes	Primary outcome:
	● Exclusive breastfeeding at 4 months postpartum (EBF4M) [phase 1 control period versus phase 2 ACE groups (combined)]
	● Secondary outcomes:
	● Exclusive breastfeeding at 1, 4, 8, 12, and 16 weeks postpartum [MW intervention group versus the VI intervention group]
	● Exclusive breastfeeding from birth to discharge
	● Time to secretory activation
	● Colostrum composition after birth: macronutrients (lactose, protein, fat content), IgA, soluble CD14, Lactoferrin, EGF, and TGF
	Other outcomes:
	● Maternal attitudes to infant feeding
	● Breastfeeding self-efficacy
	● Time from starting ACE (obtained from milk-expressing diaries) until labor
	● Post-term induction rate
	● Gestational age at birth
	● Infant admission to special care nursery

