## Data Collection and Monitoring

### Antenatal Period

All participants receive a health check via telephone between 35 and 36 weeks gestation. An ACE Study researcher administers the short health check survey to determine if a participant has developed any health conditions during pregnancy that are part of the exclusion criteria. After completion of the health check survey, participants in the intervention groups receive the ACE intervention between 36 and 37 weeks gestation. For participants in the VI group, the ACE instruction is illustrated in the ACE video where information is delivered by an IBCLC. VI group participants receive the link to the video via email. The study midwives/IBCLCs delivering the one-on-one instruction are provided with a written overview of the relevant ACE information to discuss with participants prior to conducting an instruction session. Study midwives/IBCLCs are provided with a checklist to complete during each instruction session to ensure all teaching points are covered, and the ACE technique has been demonstrated with either a knitted breast or hands-on assistance and practice (if the participant agrees). The checklist is available in the online Supplemental Material.

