During pregnancy, participants complete the mothers’ antenatal questionnaire (MAQ) online, which is used to collect demographic information, maternal health information, breastfeeding intentions, maternal attitudes towards infant feeding, and breastfeeding self-efficacy.

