### Assessment Instruments

The Iowa Infant Feeding Attitudes Scale (IIFAS), developed by Mora et al. (1999), is a reliable and valid tool used to determine maternal attitudes toward infant feeding and is included in the MAQ. The validated Breastfeeding Self-Efficacy Scale developed by Dennis and Faux (1999), is an instrument used to determine breastfeeding confidence. The shorter version, the Breastfeeding Self-Efficacy Scale-Short Form (BSES-SF; Dennis, 2003) is included in the MAQ.

Maternal secretory activation status can be assessed by maternal self-reporting of symptoms of secretory activation using the Assessment of the Onset of Lactogenesis II originally developed by Chapman and Pérez-Escamilla (2000). Maternal self-reporting of secretory activation has been shown to be a reliable indicator of secretory activation when compared with the gold standard method of test weighing an infant before and after breastfeeding to ascertain secretory activation (Rocha et al., 2020).

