The ACE Study uses a version of the two-question Assessment of Onset of Lactogenesis II adapted by Demirci et al. (2023) for use in their pilot study to determine the feasibility and potential benefits of ACE in a small sample of United States mothers. Demirci et al. determined time of secretory activation by asking participants at 1–2 weeks postpartum: “How long did it take your milk to "come in” after your baby was born (i.e., when did you notice a big increase in the amount of milk)?” Demirci et al. adapted the assessment to minimize the cumulative participant survey burden in the early postpartum period. Answer options were also adapted from a by-hour recall to a by-day recall as Demirci et al. anticipated it would be difficult for participants to recall details 1–2 weeks after birth. In the ACE Study participants are asked at the 1-week postpartum questionnaire: “How long did it take your milk to “come in” after your baby was born (i.e., when did you notice a big increase in the amount of milk and a feeling of breast fullness)?” Answers are recorded to the nearest day, that is, “1 day or less,” “2 days,” “3 days,” “4 days,” “more than 4 days,” “my milk never came in,” “I don’t remember when my milk came in.” Mothers who report that their milk came in ≤ 1 day will be considered to have early secretory activation, milk onset at 2 days, or 3 days postpartum will be considered normal secretory activation, and onset at 4 days, or more than 4 days postpartum will be considered delayed secretory activation (> 72 hr postpartum). All participants repeat the BSES-SF at 4 weeks postpartum.

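### Maternal attitude (IIFAS) is listed as an outcome of ACE, but its only scheduled measurement comes before ACE is taught

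*Protocol article*

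**What the plan says.** Table 1 lists "Maternal attitudes to infant feeding" under other outcomes. Table 4 gives the measure as the IIFAS and the comparison as "Difference, between the control group and intervention groups combined (MW and VI), scores on the IIFAS", with no assessment time.

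Under Assessment Instruments, the IIFAS "is a reliable and valid tool used to determine maternal attitudes toward infant feeding and is included in the MAQ". The paragraph on that questionnaire, at the end of the section on ACE instruction, says: "During pregnancy, participants complete the mothers’ antenatal questionnaire (MAQ) online". Attitudes and self-efficacy are both among the contents it lists. Table 3 marks the IIFAS once, at t1, which its note defines as 32–34 weeks of gestation.

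On the timing of teaching, the Antenatal Period section states that "participants in the intervention groups receive the ACE intervention between 36 and 37 weeks gestation". Table 3 marks both forms of instruction at t2, defined as 35–36 weeks. On later measurement, Assessment Instruments states: "All participants repeat the BSES-SF at 4 weeks postpartum". It says nothing comparable for the IIFAS.

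The text below Table 4 also names "maternal attitudes towards breastfeeding" among the confounders identified in advance.

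**The concern.** An outcome can carry information about an intervention only if it is measured after the intervention has had a chance to act. Here the only stated measurement comes first.

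The comparison is also between phases. Controls are recruited at each site before the intervention phase opens, so control versus combined ACE is not a concurrent, individually randomized contrast. A difference in attitude scores taken before teaching would reflect who joined in each phase, or what participants already knew about their assignment. Listed as an outcome, a recruitment imbalance could be read as ACE having improved attitudes, and a null result as ACE having left them unchanged. Neither would follow.

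The same construct is named as a confounder, a role that suits a score taken before teaching. The IIFAS is the only attitude instrument the article describes, so on a natural reading one score is given two roles, and it can properly serve in only one of them.

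**Working it through.** The plan gives no figure to reproduce. The check is one of timing.

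**Inputs**

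| Item | Timing | Source |
|---|---|---|
| IIFAS | During pregnancy, in the antenatal questionnaire | Text on that questionnaire; Assessment Instruments |
| IIFAS | t1 = 32–34 weeks, one mark | Table 3 and its note |
| ACE instruction, from the text | 36–37 weeks | Antenatal Period |
| ACE instruction, from the timeline | t2 = 35–36 weeks | Table 3 and its note |
| Start of expressing | From 37 weeks | Antenatal Colostrum Expression Instruction; Table 1 |
| BSES-SF | t1 and t5 (4 weeks postpartum), two marks | Table 3; Assessment Instruments |

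**Gap between the IIFAS and instruction**

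Shortest gap = earliest instruction − latest IIFAS. Longest gap = latest instruction − earliest IIFAS.

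- With instruction at 36–37 weeks: 36 − 34 = 2 weeks to 37 − 32 = 5 weeks.
- With instruction at 35–36 weeks: 35 − 34 = 1 week to 36 − 32 = 4 weeks.

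The text and Table 3 differ by a week on when instruction is given. The order is the same on both readings: the IIFAS comes first. Expressing starts later still, at least 37 − 34 = 3 weeks after the score.

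**Scores available after instruction**

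- IIFAS: 0 scheduled.
- BSES-SF: 1 scheduled, at t5.

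**Is the single IIFAS mark reliable?** Table 3 is imperfect as extracted: the row for exclusive breastfeeding shows no marks. The BSES-SF row, however, shows both its marks, and they agree with the text. The single IIFAS mark likewise agrees with the text, which puts the scale in an antenatal questionnaire and describes a postnatal repeat for the BSES-SF alone. The conclusion does not rest on the table alone.

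**What could a difference at t1 mean?** Table 3 places t1 under the post-allocation heading, with allocation before 34 weeks. Phase 2 participants are told their arm by email after consent. Three sources of difference remain: case mix between phases, calendar time, and knowledge of assignment. Neither the teaching nor the practice of expression is among them.

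**The case against.** The strongest reply is that this is a labelling fault of small consequence. The IIFAS appears in none of the five research questions. The planned analysis describes no model or test for it. The sentence saying that additional outcomes are recorded to see whether ACE influences them names nursery admission, gestational age, post-term induction and time to labor, but not attitudes. This is correct and limits the weight of the point. It does not remove it: Table 4 sets the IIFAS beside gestational age and nursery admission with the same between-group wording, and a reader will take it as an effect comparison.

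A second reply is that the article is condensed and a later assessment may exist elsewhere. The text says only that the questionnaire is completed during pregnancy, with no closing date, and the description of the postnatal questionnaires is not exhaustive, since it also omits the BSES-SF. A second assessment is therefore not disproved. But the article fixes both a contrast and a schedule, and the two do not fit. If a later assessment exists, Table 3 and the text need correcting instead.

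Third, the dual role as outcome and confounder is partly inferred. The confounder list names the construct and not the scale, and the adjustment set leaves other confounders open. Describing a score by group and adjusting for it in a breastfeeding model are also compatible analyses. The main point does not depend on the dual role.

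Fourth, the score may follow notification of the arm, so it could carry an effect of knowing the allocation. That is granted. It would be an anticipation effect, inseparable here from the difference between phases.

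**Conclusion.** The concern holds. As written, the IIFAS outcome cannot inform on the effect of ACE instruction or practice: the one scheduled score precedes instruction by 2–5 weeks (text) or 1–4 weeks (Table 3), and no later score is scheduled. This assumes that participants complete the antenatal questionnaire within the window in Table 3 and that no unreported repeat exists.

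The correction should be made, but its reach is limited. The IIFAS is one of the other outcomes, and the primary and secondary conclusions do not depend on it.

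**What to change.** Remove the IIFAS from the outcome lists in Tables 1 and 4. Report it by group as a baseline characteristic and, where the analysis calls for it, use it as the measure of the attitude confounder already named. Describe it as measured before instruction rather than before allocation, since some participants may know their arm when they answer. Update the registry entry to match; the article's section on amendments provides for this. The cost is wording only, and the change can be made at any time before results are reported.

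If a change in attitude is of real interest, the IIFAS could be added to the 4-week contact, where the BSES-SF is already repeated, for participants who have yet to reach it. The interpretable comparison would then be MW against VI, adjusted for the antenatal score, because those arms are randomized concurrently. That would be a new and only partly collected outcome, different from the control-versus-ACE contrast now in Table 4. It would have to be labelled as such, and it lengthens one existing contact. It is not needed to correct the plan.

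If a later IIFAS assessment is in fact being collected, state its time in Tables 3 and 4 and in the text.

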Participants are provided with an intervention pack that contains a one-page handout outlining key points to remember when practicing ACE, 15 × 1 ml syringes to collect colostrum, and a cooler bag. Intervention packs can be collected from antenatal clinics at trial sites or from the midwife/IBCLC providing the one-on-one instruction. Participants are instructed to use one or more syringes for colostrum collection per day and to keep the syringes in the fridge between uses. Participants are informed that the syringes should be labelled with the date of collection, placed in a zip lock bag, and stored in their home freezer at the end of each day. Participants are provided with a bag labeled with their name to transport the colostrum syringes to the hospital at the time of birth and advised to transport the colostrum in the provided cooler bag with a freezer block. At the trial sites, there is an ACE Study box in the freezers on the maternity wards for participants to store their antenatal colostrum. After birth, the antenatally expressed colostrum can be used to supplement breastfeeding if required. If breastfeeding is going well, expressed colostrum may not be required. If colostrum syringes are not required at birth, they can be stored for 3 months in the freezer section of a refrigerator with a separate door, or 6–12 months in a deep freezer. If thawed, colostrum should be used within 4 hours if kept at room temperature, or within 24 hours if kept in the refrigerator (Australian Breastfeeding Association, 2022).

If COVID-19-related issues mean that in-person consultations are not possible, one-on-one sessions with a midwife/IBCLC may take place online. This will be noted in the data collection and when reporting findings.

Participants in the MW and VI groups are provided with direct access to an electronic milk expressing diary via Research Electronic Data Capture (REDCap; Harris et al., 2019). The diary can be accessed by email link sent daily to participants and is used to record the date they start ACE, the time they express, the volume of colostrum expressed per day, and reasons for not expressing if that occurs. The milk expressing diary has a section for additional comments where participants are encouraged to record their feelings about expressing (feelings about obtaining colostrum or not), the number of times they watch the video at home (if in the VI group), and the absence or presence of uterine contractions.

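### Two of the other outcomes in Table 4 cannot show an effect of ACE as defined: controls have no recorded ACE start date, and the IIFAS is taken only before instruction

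*Protocol article*

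**What the plan says.** **Time from starting ACE until labor.** In Table 4 (Outcomes/Measurement) the row is labelled "Time from starting ACE (obtained from expressing diaries) until labor", and the contrast is "Difference, between the control group and intervention groups combined (MW and VI) in time from starting ACE until labor". Under Antenatal Colostrum Expression Instruction, "Participants in the MW and VI groups are provided with direct access to an electronic milk expressing diary", and that diary "is used to record the date they start ACE, the time they express, the volume of colostrum expressed per day". Controls receive standard maternity care (Choice of comparators).

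The paragraph that introduces Table 4 names four outcomes: special care nursery (SCN) admission, gestational age at birth, post-term induction and time from starting ACE until labor. It says they "will be recorded for MW and VI group participants to determine if ACE influences these additional outcomes".

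**IIFAS.** Table 4 gives the outcome as "Difference, between the control group and intervention groups combined (MW and VI), scores on the IIFAS". Assessment Instruments says that the IIFAS "is a reliable and valid tool used to determine maternal attitudes toward infant feeding and is included in the MAQ", the MAQ being the questionnaire completed during pregnancy. Table 3 marks the IIFAS once, at t1, which its note defines as 32–34 weeks. The only scale said to be given again is the other one: "All participants repeat the BSES-SF at 4 weeks postpartum". The text after Table 4 also lists maternal attitudes towards breastfeeding among the potential confounders chosen in advance.

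**The concern.** A between-group outcome needs two things: it must be defined and recorded in both groups, and it must be measured after the intervention could have acted. The time-to-labor row fails the first test and the IIFAS row fails the second.

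The Background cites a historical worry that ACE may affect hormones that promote labor, and time to labor is the listed outcome whose name comes closest to it. As defined it yields no comparison with controls. For the IIFAS, controls at each site are recruited in an earlier phase than the ACE participants. The comparison therefore sets pre-instruction scores from two recruitment periods side by side under the label of an outcome. An analysis plan cannot repair either row by method alone, because the data each contrast needs are not scheduled to be collected.

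**Working it through.** No sample size or power figure is at issue. The check sets the statements side by side.

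**1. Is the time origin recorded in both groups?**

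| Element | Control | MW and VI |
|---|---|---|
| ACE instruction | None; standard care | Yes |
| Expressing diary (source of the start date) | Not provided | Provided |
| Date of labor (medical data) | Available | Available |
| Time from ACE start to labor | No recorded origin | Computable |

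Controls with a diary-recorded start date: 0 of the planned 315 (Sample Size). The contrast is a difference between a quantity that exists in the ACE groups and one that is not recorded in controls.

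**2. Are the other three outcomes recorded in controls?** The introductory sentence mentions only MW and VI participants. Table 4 compares SCN admission, gestational age and post-term induction with controls and takes all three from medical data. The Medical Data section obtains obstetric outcomes from the records of consenting participants, without restriction by group. The sentence and the table differ, but two of the three places point to recording in everyone.

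**3. Is the IIFAS measured after the intervention?**

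- IIFAS: 32–34 weeks (Table 3, t1).
- Instruction: 35–36 weeks by Table 3 (t2), or 36–37 weeks by the Antenatal Period section.
- Start of expressing: from 37 weeks.

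Gap from IIFAS to instruction on Table 3 timing: shortest 35 − 34 = 1 week, longest 36 − 32 = 4 weeks. On the Antenatal Period timing: shortest 36 − 34 = 2 weeks, longest 37 − 32 = 5 weeks. Gap from IIFAS to the earliest expressing: 37 − 34 = 3 to 37 − 32 = 5 weeks.

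The IIFAS comes first under either window. The two windows should be reconciled, but the conclusion does not depend on which applies. Scheduled IIFAS assessments after instruction: 0. Scheduled BSES-SF assessments after instruction: 1, at 4 weeks postpartum (Table 3, t5).

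**4. Could a second IIFAS mark have been lost from Table 3?** The exclusive breastfeeding row has no marks in the text at hand, so the table may not have reproduced perfectly. However, the BSES-SF row shows both of its marks, the prose confirms that repeat, and nothing in the article mentions a second IIFAS.

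**The case against.** The strongest reply is that little depends on either row. Both are in the lowest tier of outcomes. Planned Data Analysis names only SCN admission and gestational age as other outcome variables, and gives no test for the IIFAS or for time to labor. The time-to-labor contrast may be row wording repeated by habit, since the introductory sentence limits that outcome to MW and VI. Much of this stands, and it rules out several stronger readings that a reader might infer.

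- **That the labor-onset safety question goes unanswered.** It does not. The Background describes the earlier trial's safety evidence as neonatal intensive care admission and mean gestational age at birth. This trial compares gestational age, SCN admission and post-term induction with controls.
- **That control data on those outcomes will be missing.** The introductory sentence does not say only MW and VI, and Medical Data and Table 4 imply recording in all groups. This is loose drafting.
- **That the expected IIFAS difference is zero by construction.** Table 3 places allocation before 34 weeks, and participants are told their arm by email after consent. Some may know their group when they complete the IIFAS, and that could shift scores before any instruction.
- **That a baseline gap will be reported as an ACE effect.** The article describes no IIFAS analysis, so this is a risk created by the label, not a stated plan.
- **That no control ever expresses.** The Background notes that ACE brochures are available online. The documents support only that no start date is recorded for controls.

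Listing attitudes as a confounder is not itself a fault, because antenatal measurement suits that use. What remains is one contrast that cannot be computed and one pre-instruction scale labelled as an outcome.

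**Conclusion.** Both defects hold, at modest weight. The control-versus-ACE contrast in time from starting ACE until labor cannot be computed, because no control has a recorded origin. The control-versus-ACE IIFAS difference cannot show an effect of ACE instruction or practice, because the only scheduled score precedes instruction by 1 to 5 weeks. It can show phase differences, recruitment differences or the effect of knowing one's allocation.

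The IIFAS conclusion rests on Table 3 and its note, since the text alone says only that the MAQ is completed during pregnancy. The time-to-labor conclusion rests on the diary being the only source of the start date, as Table 4 states.

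The primary and secondary outcomes are unaffected, and gestational age at birth largely covers the labor-onset question. The rows should still be corrected, since the article states them affirmatively and correction is nearly free.

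**What to change.** **Time to labor.** Choose one of two options.

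- Keep the outcome as named and limit it to a description of the ACE groups or an MW-versus-VI comparison.
- Redefine it with an origin that exists in every group, for example a fixed gestational age to onset of labor, taken from medical records. This adds only labor onset, as distinct from birth, to what gestational age at birth already gives.

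The first option costs one changed table cell. The second costs one derived variable, provided the records hold the date of labor onset for controls as they must for the ACE groups.

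**Introductory sentence.** Reword it so that SCN admission, gestational age and post-term induction are stated to be recorded in controls as well. No new data collection is implied.

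**IIFAS.** Move it from the outcomes to the baseline covariates, in line with its listing as a potential confounder. This costs only wording. The alternative is to repeat it at 4 weeks postpartum with the BSES-SF, at the cost of a slightly longer questionnaire. That alternative has a limit. Controls are recruited first and complete 4 months of observation before Phase 2 begins (note to Figure 2). At any site already in Phase 2, controls have passed the 4-week point, so a repeat added now would have no control scores there. The article does not say which sites are in which phase, so check this before choosing.

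The article says that recruitment is ongoing and that protocol changes are notified through the registry, so these corrections have a route.
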